### Sample size

Sample size was calculated based upon the primary outcome, and the initial calculation was done without regard for clustering. A change in the quality score of 10% was determined to be clinically interesting. Setting the significance level at 0.05 and using PASS 2008 (NCSS, LLC, Kaysville, UT, USA) for the calculation provides that the study would require 855 patients in the control and 855 in the intervention group, for an 80% power to detect a 10% difference between the groups.

To correct for clustering, the design effect (DE) may be calculate as:

DE = 1 + *ρ*(*m*-1)

where *ρ* denoted the intracluster correlation coefficient (ICC) and *m* is the size of each cluster [36]. No ICC for equivalent designs was identified from literature searches. Reviewing primary care-based interventions from the literature [37-39], an expected ICC ranging from 0.001 to 0.08 does not seem improbable, giving a DE of 1.15 and 12.9, respectively, for a cluster size of 150 patients. Because only 14 GP clinics were available for randomization, further inflation of the number of clusters to achieve higher power was not possible, although this could have been advisable [40].

Based upon a review of patient data at UNN Harstad from 2008, the study is expected to achieve this relatively high inclusion number by recruiting over a two-year period (personal data).

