### Statistical methods

We will collect the following baseline characteristics:

• patient age (mean and confidence interval) and sex (number and percentage)

• practice list size (median and interquartile range, or mean and confidence interval if normally distributed)

• referral type - electronic or paper (number and percentage)

• referred by - GP or other doctor (number and percentage).

For the primary outcome (quality score), we will calculate adherence scores as described above and compare between treatment arms. We expect substantial variation in cluster size. Because of the small number of clusters, analysis based upon the cluster level was considered [41]. However, as there is no prior accurate estimate of variation between clusters, weighting for cluster size could not be achieved [41]. To offer increased precision and take into account between-cluster variation, random effects linear regression will be used [42] to generate estimates of intervention effect. It has been suggested that this can be used for studies with as few as 10 clusters [36]. The estimated effect and confidence intervals will be reported. A *P*-value <0.05 will be regarded as statistically significant. Intention to treat analysis will be employed.

The referrals will be scored using a simple scoring system related to the referral templates. Each unit of information specified in the referral template (for example, presence of weight loss specified) will provide one point in the scoring system, with no weighting applied. Scores will be compared between the groups as noted above.

For outcome severity, random effects linear regression will be used, with the severity group score as a categorical variable, and the relationship compared between the intervention and control group.

In the questionnaire, answers noted as ‘not applicable’ or no answer will be counted as missing data. The questionnaire will be scored according to a pre-set scoring system. Scores will be analyzed using the regression technique outlined above. The data will also be analyzed to determine if factors such as self-perceived health, age, gender, and education level have an impact on patient experience.

The trial will be reported according to the CONSORT standards for reporting cluster randomized trials [43].

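### The stated 80% power is for a design without clustering: design effects of 1.15 to 12.9 are computed but never applied, so the cluster trial's power is not given

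*Protocol article*

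**What the plan says.** All the figures are in the protocol article, Methods, Sample size. The section is open about its starting point: "Sample size was calculated based upon the primary outcome, and the initial calculation was done without regard for clustering". The alpha is given ("Setting the significance level at 0.05"), and the resulting requirement is that "the study would require 855 patients in the control and 855 in the intervention group". The power attached to that number is 80%, for a difference of 10% in the quality score.

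It then introduces the usual design-effect formula as the means of correcting for clustering. It takes an ICC range of 0.001 to 0.08 from other primary care trials and evaluates the formula, "giving a DE of 1.15 and 12.9, respectively, for a cluster size of 150 patients". It adds that only 14 clinics were available, so clusters could not be added, although that might have been advisable. It closes by saying that "the study is expected to achieve this relatively high inclusion number by recruiting over a two-year period". The only inclusion number given in the section is 855 + 855.

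The Statistical methods section plans a random effects linear regression, which does account for clustering, and notes: "We expect substantial variation in cluster size".

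**The concern.** The correction is set up and then left unused. After the two design effects appear, no inflated target, revised power or detectable difference follows. The single power statement therefore describes a different design from the one being run and from the model that will analyse it.

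What is at stake is how the result is read. If the primary comparison is null, the 80% invites the conclusion that a 10% improvement was fairly tested and not found. With seven clinics per arm and an ICC towards the upper end of the protocol's own range, that may not be so. The protocol gives the reader no means of judging, because the inputs behind the 855 are missing too.

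**Working it through.** **Inputs from the protocol.** 855 per arm; 80% power; alpha 0.05 (sidedness not stated, two-sided assumed); ICC 0.001 to 0.08; cluster size 150; 14 clinics, 7 of them intervention (Abstract), so 7 control; outcome an adherence score from 0 to 100 (Outcomes). The SD, the baseline score and whether the 10% is absolute or relative are not stated.

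**1. The protocol's design effects reproduce.** DE = 1 + ICC × (m − 1).
- 1 + 0.001 × 149 = 1.149
- 1 + 0.08 × 149 = 12.92

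**2. The 855 cannot be reproduced.** The standardised difference that gives 80% power at 855 per arm is d = (1.96 + 0.8416) × √(2/855) = 0.1355.
- Read as 10 absolute points, SD = 10/0.1355 ≈ 74. A score bounded by 0 and 100 cannot have an SD above about 50. Even at SD 50 only 393 per arm would be needed, and at SD 20 only 63.
- Read as a relative 10%, d = 0.10 × mean/SD, so SD ≈ 0.738 × baseline mean. An assumed mean of 40 would need an SD of about 29.5, which is possible, but the protocol gives neither figure.

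**3. Power with the design effect applied, taking 855 for 80% at face value.** Power = Φ(0.1355 × √(855/(2 × DE)) − 1.96).

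| ICC | m | DE | Effective n per arm | Power |
|---|---|---|---|---|
| 0.001 | 150 | 1.149 | 744 | 74.3% |
| 0.01 | 150 | 2.49 | 343 | 42.7% |
| 0.05 | 150 | 8.45 | 101 | 16.0% |
| 0.08 | 150 | 12.92 | 66 | 11.9% |
| 0.001 | 122 | 1.12 | 763 | 75.4% |
| 0.08 | 122 | 10.7 | 80 | 13.5% |

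The size 122 is 1,710/14; 150 per clinic would mean 14 × 150 = 2,100 patients. A t reference on 12 df (14 clinics − 2) lowers the range to 67% to 11% at m = 150 and 68% to 12% at m = 122. Unequal clinic sizes lower it further: with an assumed coefficient of variation of 0.6, m = 122 and ICC 0.08, DE = 1 + ((1 + 0.36) × 122 − 1) × 0.08 = 14.2, and power is 10% to 11%.

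**4. What more patients could do.** Simple inflation gives 855 × 1.149 ≈ 983 and 855 × 12.92 ≈ 11,047 per arm. With 7 clinics per arm, however, the effective n cannot exceed 7/ICC. At this d, 80% is out of reach for any number of patients once the ICC exceeds 7/855 = 0.0082. At ICC 0.08 the cap is 7/0.08 = 87.5 per arm, or about 14% power.

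**5. The same target under a different assumption.** Suppose the 10% is absolute and the SD is 20 to 30 points (assumed, not in the protocol). With 855 per arm, m = 122 and t on 12 df:
- ICC 0.08: power about 83% (SD 20) to 49% (SD 30)
- ICC 0.02 or less: about 93% or more, even at SD 30

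**The case against.** The best defence is disclosure. The section says that clustering was left out, shows a design effect as large as 12.9, and concedes that more clinics might have been advisable. The Discussion adds that the cluster design is statistically less efficient. A reader might infer from the unapplied design effects that the authors overlooked clustering or concealed it. The text does not support that, and the planned analysis models clustering and reports confidence intervals, so neither bias nor an inflated type I error follows. What the disclosure does not supply is the consequence: nowhere is the 80% withdrawn or replaced.

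A reader might also infer that the trial's power simply is 74% down to 12%. The documents do not support that either. The range depends on a standardised difference back-solved from 855, and under the absolute reading that difference is impossible. With a plausible SD, power could exceed 80% over much of the ICC range. This objection stands in full and makes the range conditional.

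The gap between 150 and 122 per clinic is minor. The 150 is only the size at which the formula is evaluated, and 855 × 1.149 gives about 983 per arm, or about 140 per clinic, which is not far off. If 2,100 patients were recruited, power at ICC 0.001 would be about 82.5% even at d = 0.1355, although still about 13.7% at ICC 0.08.

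Finally, this is not a detail that the article could leave to a fuller document. The calculation is presented here and stops before its last step.

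**Conclusion.** The concern holds as an unfinished calculation. The stated arithmetic is correct, but the only power figure does not belong to the cluster design, and the design effects that would have changed it are not used.

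The size of the shortfall is conditional. If 855 per arm gives 80% under independence (two-sided 5%, equal clusters), 1,710 patients do not reach 80% anywhere in the protocol's ICC range: about 74% to 12% at 150 per clinic and 75% to 13.5% at 122. Whether that premise is true cannot be checked without the SD and the meaning of the 10%. Under an assumed SD of 20 to 30 points and an absolute 10%, power at ICC 0.08 would be about 83% to 49%. Confidence is high that the power was not restated; it is not high for any single power figure.

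**What to change.** Keep the 14 clinics and the recruitment target, and rewrite the power statement in the Sample size section:

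- State the SD assumed for the quality score and whether the 10% is absolute or relative (with the baseline score if relative). Without these a clustered table would rest on an effect size that cannot be verified.
- Replace the 80% with power and detectable difference for 7 clinics per arm at several ICCs from 0.001 to 0.08, for example 0.001, 0.02, 0.05 and 0.08.
- Use a cluster size that agrees with the target (about 122 for 1,710 patients), allow for unequal clinic sizes through DE = 1 + ((1 + CV²) × m − 1) × ICC, and use a t reference with about 12 df.
- Say explicitly that 80% holds only without clustering, and that a null result will be interpreted by its confidence interval.

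The cost is rewording and one recalculation. No extra patients or clinics are needed. The stated power may become less favourable, depending on the SD.

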### Outcomes

The primary outcome will be a quality indicator score compared between the intervention and the control group. The quality indicators have been generated from previous international quality assessment tools and national and international treatment guidelines. Some adaptation to locally accepted practice has been made, as demonstrated by others when quality indicators are used in a new context [32]. Each patient care process will be scored according to the criteria. Scoring will be done by a panel of specialists blinded to the intervention status of the patient. We will calculate the quality score as adherence scores (number of quality criteria met divided by number of applicable criteria expressed as a percentage) as illustrated by Ashton *et al*. [33]. If a criterion is applicable, but no information can be found (applicable, but not answerable), it will be noted ‘not met’ for statistical purposes [34]. Weighting of the criteria based upon clinical importance will not be used, as this adds complexity without adding much to the clinical findings, a finding discussed by Lyons and Payne in 1975 [35]. The scores will be compared between the intervention and control groups.

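### If the 10% target means 10 percentage points, 855 patients per arm is impossible on a 0–100% score; the target and the calculation need to be restated

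*Protocol article*

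**What the plan says.** The Outcomes section defines the primary outcome for each patient as an adherence score, "number of quality criteria met divided by number of applicable criteria expressed as a percentage". It therefore runs from 0 to 100. Statistical methods analyses it by random effects linear regression, that is, as a continuous mean.

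The Sample size section bases the calculation on this outcome and says the initial calculation took no account of clustering. It sets the target: "A change in the quality score of 10% was determined to be clinically interesting". The other inputs are "Setting the significance level at 0.05 and using PASS 2008", and the result is that "the study would require 855 patients in the control and 855 in the intervention group, for an 80% power to detect a 10% difference".

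Design effects of 1.15 and 12.9 follow, for intracluster correlations of 0.001 and 0.08 and 150 patients per cluster. They are not described as part of the 855. The 10% is not labelled absolute or relative.

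**The concern.** When an outcome is itself a percentage, a 10% change in it is most naturally read as 10 percentage points. A 0–100 scale limits how variable the score can be, and so limits how many patients a 10-point difference can require. The stated 855 is more than twice that limit.

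This is the trial's only sample-size figure, and it supports a two-year recruitment plan. If the target, the scale and the number do not belong together, a reader cannot tell whether the difference judged clinically interesting is 10 points or something nearer 5. That matters when a null result, or a small significant one, has to be interpreted.

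**Working it through.** **Inputs from the article.** Score bounded by 0 and 100 (Outcomes); difference 10%, significance level 0.05, power 80%, 855 per arm, clustering ignored (Sample size). **Assumed:** two-sided test, as sidedness is not given. No standard deviation (SD) or baseline is given, so both are left free within what the scale allows.

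**1. Trying to reproduce 855 with a 10-point difference.** For two means,

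n per arm = 2 × (1.96 + 0.8416)² × (SD/δ)² = 15.70 × (SD/δ)².

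Setting n = 855 gives SD/δ = √(855/15.70) = 7.38. With δ = 10, SD = 73.8 points.

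**2. The ceiling.** A score between 0 and 100 with mean m has SD of at most √(m(100 − m)), which peaks at 50 when m = 50. So 73.8 cannot occur. The unclustered requirement for 10 points is:

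| SD (points) | n per arm |
|---|---|
| 20 (assumed) | 63 |
| 25 (assumed) | 99 |
| 30 (assumed) | 142 |
| 50 (maximum) | 393 |

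Treated as two proportions, the worst case (45% v 55%) needs 392 per arm, or 412 with continuity correction.

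**3. Changing one other input at a time.** The implied SD is 83.2 if one-sided, 63.8 at 90% power, 57.4 at 95% power, and 52.2 if 855 is the total for both arms. All exceed 50. As two proportions at 90% power with continuity correction, 45% v 55% needs only 544 per arm.

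**4. Route A: the 10% is relative.** Then δ = 0.1 × m, and 855 requires SD = 7.38 × 0.1 × m = 0.738 × m.

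| Baseline mean | Target (points) | SD needed | Maximum SD |
|---|---|---|---|
| 40 | 4.0 | 29.5 | 49.0 |
| 50 | 5.0 | 36.9 | 50.0 |
| 60 | 6.0 | 44.3 | 49.0 |
| 70 | 7.0 | 51.7 | 45.8 |

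The limit is where 0.738²m² = m(100 − m), so m = 100/1.545 = 64.7%. The largest possible target on this route is therefore about 6.5 points. A yes/no calculation also comes close: 64% v 70.4% needs 844 per arm, or 875 with continuity correction.

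**5. Route B: 855 already contains a design effect.** The quoted values are 1 + 0.001 × 149 = 1.149 and 1 + 0.08 × 149 = 12.92, which match the article. Dividing, 855/12.92 = 66.2 effective patients per arm, which for 10 points gives SD = 10 × √(66.2/15.70) = 20.5. The smallest design effect that would work, at SD 50, is 855/393 = 2.18, so the lower quoted value of 1.15 is not enough.

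**6. What 855 per arm would give for 10 points** (normal approximation, SDs assumed):

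| SD | Power at DE 1.149 | Power at DE 12.92 |
|---|---|---|
| 20 | >99% | 82% |
| 25 | >99% | 63% |
| 30 | >99% | 48% |
| 50 | 97% | 21% |

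With no clustering and SD 50, power is 98.5% and the difference detectable with 80% power is 50 × 2.8016 × √(2/855) = 6.8 points.

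**The case against.** The best defence is that the text does not say percentage points. A 10% change in a score can mean a relative change, and Route A then gives 855 on the continuous score with the two-means formula. That fits both the outcome definition and the planned linear regression, for any baseline mean up to about 64.7%. This stands. A reader might infer that 855 cannot follow from the stated target on any reading, or that it needs the score to be collapsed to one yes/no per patient. The article supports neither: the impossibility is conditional on the absolute reading, and no binary outcome is needed.

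It is also fair that a condensed article may leave the SD, the baseline and the software procedure to a fuller document. Their absence is not the point here. On the absolute reading no SD rescues the number, so the conflict lies among figures that the article does state.

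Finally, on that reading the error asks for more patients than the unclustered target needs, and what limits power in this trial is clustering among 14 clinics. That is correct, and it limits the consequence. It does not make 855 a safe margin, because the surplus exists only before the design effect is applied.

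**Conclusion.** The point holds in conditional form. Read as 10 percentage points, the stated 855 per arm is impossible: it implies an SD of 73.8 against a ceiling of 50, and it is at least 855/393 = 2.2 times the largest number the scale allows. At assumed SDs of 20 to 30 the ratio is about 6 to 14 (855/142 to 855/63). These ratios apply only to the absolute reading.

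The two routes that do reach 855 each require a change to the text. If the 10% is relative, the target is less than about 6.5 points and a baseline has to be stated. If a design effect is already included, the statement that clustering was ignored is wrong. The article does not show which route was taken, and a plain input error cannot be excluded.

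A reader might also infer that the trial is oversized or, from the larger design effect, undersized. Neither follows. For a 10-point difference, power with 855 per arm runs from 21% to more than 99% across the quoted design effects and SDs of 20 to 50, and nothing in the article narrows that range.

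**What to change.** - State the target as absolute percentage points, or as relative together with its baseline mean.
- Recompute the unclustered number with the two-means formula, which matches the planned linear regression, from an SD that the scale allows.
- State the power, or the detectable difference in points, that 855 per arm gives across the quoted design effects of 1.15 to 12.9.
- If 855 came from a two-proportion calculation, say so. If it already includes a design effect, correct the sentence that says clustering was not considered.

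The Pilot study section reports that all protocol data were collected on the first 20 patients. A blinded pooled SD from them may be obtainable, but 20 patients spread over four diagnostic groups give an imprecise value, so results should be shown over a range of SDs.

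The cost is one recalculation and a reworded paragraph. Recruitment, the number of clinics and the analysis method need not change.

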### Blinding

The referring GP cannot be blinded to the trial, as the intervention is actively used by the GP. The patient will not be aware of the intervention, but no active effort has been made to keep the patients blinded. The patients will be mixed with the general caseload to avoid bias in the treatment process at the hospital. For the GPs that use the electronic referral template, this usage will be visible to the hospital doctor in the presentation of the referral letter on the computer, but for the majority of the cases the hospital doctor will be blinded to the intervention status of the patient. The outcome assessors will be blinded.

### Data gathering

Data will be extracted by both automated computer reports (for example, waiting times, number of appointments) and manual chart review (for example, PPV, group of final diagnosis). Data will be collected after the process of care that the referral initiated is completed.

### Statistical methods

We will collect the following baseline characteristics:

• patient age (mean and confidence interval) and sex (number and percentage)

• practice list size (median and interquartile range, or mean and confidence interval if normally distributed)

• referral type - electronic or paper (number and percentage)

• referred by - GP or other doctor (number and percentage).

For the primary outcome (quality score), we will calculate adherence scores as described above and compare between treatment arms. We expect substantial variation in cluster size. Because of the small number of clusters, analysis based upon the cluster level was considered [41]. However, as there is no prior accurate estimate of variation between clusters, weighting for cluster size could not be achieved [41]. To offer increased precision and take into account between-cluster variation, random effects linear regression will be used [42] to generate estimates of intervention effect. It has been suggested that this can be used for studies with as few as 10 clusters [36]. The estimated effect and confidence intervals will be reported. A *P*-value <0.05 will be regarded as statistically significant. Intention to treat analysis will be employed.

The referrals will be scored using a simple scoring system related to the referral templates. Each unit of information specified in the referral template (for example, presence of weight loss specified) will provide one point in the scoring system, with no weighting applied. Scores will be compared between the groups as noted above.

For outcome severity, random effects linear regression will be used, with the severity group score as a categorical variable, and the relationship compared between the intervention and control group.

In the questionnaire, answers noted as ‘not applicable’ or no answer will be counted as missing data. The questionnaire will be scored according to a pre-set scoring system. Scores will be analyzed using the regression technique outlined above. The data will also be analyzed to determine if factors such as self-perceived health, age, gender, and education level have an impact on patient experience.

The trial will be reported according to the CONSORT standards for reporting cluster randomized trials [43].

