**Methods:**

A cluster randomized trial, with the general practitioner office as the unit of randomization, has been designed to evaluate the effect of a referral intervention on the quality of health care delivered. Referral templates have been developed covering four diagnostic groups: dyspepsia, suspected colonic malignancy, chest pain, and chronic obstructive pulmonary disease. Of the 14 general practitioner offices primarily served by University Hospital of North Norway Harstad, seven were randomized to the intervention group. The primary outcome is a collated quality indicator score developed for each diagnostic group. Secondary outcomes include: quality of the referral, health process outcome such as waiting times, and adequacy of prioritization. In addition, information on patient satisfaction will be collected using self-report questionnaires. Outcome data will be collected on the individual level and analyzed by random effects linear regression.

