### Randomization

The GP clinics were randomized stratified by location, to ensure adequate selection of cases and equal sociodemographic background data. Five of the centers are larger town-based centers and nine are smaller, more rural centers. The location of the center was not expected to influence the outcome variables. Initially, two centers approached declined the invitation to participate in the study, and therefore two additional GP clinics were randomly selected, as illustrated by Figure 1.

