**Figure 1 F1:**
[figure not shown]
**Flow chart of randomization process.** ‡ From the four rural clinics initially randomized to the intervention group, two clinics refused. Therefore two additional rural clinics, from the five rural clinics initially randomized to the control group were randomized, and consented to, the intervention.

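### The primary model names no term for the location stratum or for the diagnostic group behind each score, and the referral-quality score has no denominator

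*Protocol article*

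**What the plan says.** - **Design.** The Randomization section states "The GP clinics were randomized stratified by location", and gives the strata: "Five of the centers are larger town-based centers and nine are smaller, more rural centers". It adds: "The location of the center was not expected to influence the outcome variables".
- **Allocation.** The abstract says that of the 14 offices "seven were randomized to the intervention group". The caption to Figure 1 reports: "From the four rural clinics initially randomized to the intervention group, two clinics refused". Two rural clinics from the five first drawn to control then took their place.
- **Primary outcome.** From the abstract: "The primary outcome is a collated quality indicator score developed for each diagnostic group". The Outcomes section defines the score as criteria met over applicable criteria, as a percentage.
- **Primary analysis.** Statistical methods compares scores between arms and says that "random effects linear regression will be used [42] to generate estimates of intervention effect". The stated reason is between-cluster variation. No fixed effect other than arm is named.
- **Referral quality (secondary).** Each item specified in a template "will provide one point in the scoring system, with no weighting applied", and the scores are compared between groups in the same way. No denominator is given.

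**The concern.** Two features that structure the data, the randomisation stratum and the diagnostic group, do not appear in the analysis as described.

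For location, stratified allocation removes most of the town-rural difference from the true sampling variation of the contrast. A model without the stratum still counts that difference as between-clinic variance. If location matters, the standard error is then too large, in a trial that by its own account could not add clusters.

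For diagnostic group, the pooled percentages come from four different indicator sets whose means need not agree. Randomising 14 clinics does not fix the case mix, and patients are recruited after randomisation; the Discussion itself raises the risk of different cohorts in the two arms. The listed baseline characteristics do not include diagnostic group either, so an imbalance would not be visible from that list.

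For referral quality, a raw count of items has a different maximum for each template if the templates differ in length. Diagnostic mix alone could then move the arm means.

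**Working it through.** The documents give no effect of location or diagnostic group, so there is no figure of the plan's own to reproduce on this point. The check has five steps.

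**1. Allocation.** Inputs: 14 clinics, 5 town and 9 rural (Randomization); 7 in intervention (abstract); 4 rural clinics drawn to intervention (Figure 1 caption).
- Town clinics in intervention = 7 − 4 = 3; in control = 5 − 3 = 2. Rural clinics: 4 and 5.
- The two refusing clinics were replaced by two other rural clinics, so the intervention count stays at 3 town + 4 rural.
- Both strata are odd, so 3/2 and 4/5 is the closest balance possible with 7 clinics per arm.
- The town split is inferred; the article does not state it.

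**2. Shift from location.** Shift = (town share in intervention − town share in control) × D, with D the town-rural difference in mean score (unknown).
- Seven against seven: 3/7 − 2/7 = 0.143. D = 5 gives 0.7 points; D = 10 gives 1.4.
- Refusing clinics not analysed (seven against five): 3/7 − 2/5 = 0.029.
- Weighted by patients, with town clinics k times the rural size, the factor is 3k/(3k+4) − 2k/(2k+5): 0.143, 0.156, 0.147 and 0.123 at k = 1, 2, 3 and 5. Without the refusing clinics, 3k/(3k+4) − 2k/(2k+3) runs from 0.029 down to 0.020. Weighting therefore does not reliably enlarge the shift.

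**3. Effect on the test.** Cluster means were simulated under the stratified 3/2 and 4/5 allocation (20,000 runs). The cluster-mean SD was assumed to be about 3.5 points. Each run was analysed by least squares on the 14 means, with and without a location term (11 and 12 degrees of freedom), as a stand-in for the random effects model.

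| Assumed D | Type I error without location | Type I error with location |
|---|---|---|
| 0 | 0.047 | 0.048 |
| 3 | 0.038 | 0.049 |
| 5 | 0.026 | 0.051 |
| 10 | 0.004 | 0.052 |

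For an assumed true effect of 6 points, power with the location term is about 82% whatever D is. Without it:
- D = 0: about 84%, so the term costs about 2 percentage points.
- D = 5: about 79% if town clinics score higher, about 57% if they score lower.
- D = 10: about 56% and about 12%.

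**4. Shift from diagnostic group.** Shift = difference in case mix × difference in group means. Both are assumptions.
- 5 percentage points × 10 score points = 0.5 points.
- 10 × 20 = 2 points, one fifth of the 10% target in the Sample size section if that target is read as points.
- 20 × 20 = 4 points.

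**5. Precision from diagnostic group.** Assume group means of 50, 60, 70 and 80 and a within-group SD of 20.
- The variance of the means is 125, and group explains 125/(125 + 400) = 24% of patient-level variance.
- With 150 patients per clinic and the article's ICC range, the patient-level share of cluster-mean variance, [(1 − ICC)/150] / [(1 − ICC)/150 + ICC], is 87% at ICC 0.001 and 7% at 0.08.
- If all group variance lies within clinics, the standard error falls by 1 − √(1 − 0.87 × 0.238) = 11% and 1 − √(1 − 0.07 × 0.238) = about 0.9%.

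The gain in precision may therefore be slight. Protection against case-mix shifts is the stronger reason for the term.

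**The case against.** The strongest reply is that a covariate list is what an article leaves to the analysis plan, which is not shown. The section names a model class and never calls it unadjusted. That stands against saying that the authors decided to leave the terms out. It does not dispose of the point: the same section names regressors elsewhere (severity group for waiting time; self-perceived health, age, gender and education for patient experience) but none for the primary outcome, and someone following it as written would fit arm alone.

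A reader might also infer that the arms are unequal on location by design, and that false positives follow. The documents do not support this. The split is the closest that odd strata allow and nearly vanishes if the refusing clinics are not analysed. The article expects no location effect, although it shows no data for that. The simulated test without the term is conservative.

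The primary score is already a percentage of applicable criteria, so the four indicator sets share a scale. That stands, but a common scale does not give common means. Recruitment follows the same procedure in both arms, which reduces but does not exclude differences in case mix.

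For referral quality, template lengths are not given, so it cannot be said that the scales do differ. The rule of one point per item without a denominator is nevertheless stated text, and it differs from the rule used for the primary score.

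**Conclusion.** The point holds as a gap in specification that is worth closing before analysis. Diagnostic group is the stronger half, because nothing in the design controls case mix; its size is unknown, with 2 points as an illustration under the assumptions above. Location is the weaker half: a shift of about 0.14D at most in the plain clinic count (0.12 to 0.16 by patient weight, 0.02 to 0.03 without the refusing clinics), and mainly a loss of power if town and rural clinics differ. If they do not differ, leaving location out costs nothing. The power and type I error figures rest on the assumed cluster-mean SD and on an analysis of equally weighted cluster means. The referral-quality point is conditional on the four templates having different numbers of items.

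**What to change.** - State location (town/rural) and diagnostic group (four levels) as fixed effects in the primary random effects model and in the corresponding secondary models.
- Assign diagnostic group by the same rule in both arms, and add it to the baseline table.
- Score referral quality as the percentage of the relevant template's items present, in place of raw points.
- Adjustment for age and sex, which are already collected, is optional.

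The cost is wording. Location and diagnostic group are already known for each patient. The location term takes one cluster-level degree of freedom (12 to 11) and, if location has no effect, about 2 percentage points of power in the simulated setting. The stated sample size does not change.
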